### 6.2 Secondary objectives

#### 6.2.1 Efficacy

To determine if ISTp-DP compared with IPTp-SP in the second and third trimesters of pregnancy is associated with:

- A decrease in the prevalence of placental malaria at delivery
- An increase in the mean duration of pregnancy or a reduction in the prevalence of pre-term birth

- An increase in mean birth weight or a reduction in the prevalence of low birth weight
- A decrease in stillbirths, neonatal deaths or perinatal death
- A decrease in pregnancy loss in the second and third trimesters
- An increase in mean haemoglobin levels or decrease in any anaemia, moderate anaemia and severe anaemia at delivery
- A decrease in the prevalence of peripheral parasitaemia at delivery
- A decrease in the incidence of clinical malaria episodes in pregnancy
- A decrease in the incidence of peripheral parasitaemia in the third trimester of pregnancy
- An increase in mean haemoglobin levels or decrease in any anaemia, moderate anaemia and severe anaemia during the third trimester of pregnancy
- A decrease in the prevalence and incidence of clinical malaria or symptomatic anaemia in infants by seven days and six to eight weeks

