## 7 Trial design

### 7.1 Overview of design

This will be a two-arm randomized controlled trial conducted at three or more sites in southern Malawi with high levels of SP resistance and high ITN coverage. Enrolment will be stratified by gravidity group (stratified design); one for primi and secundigravidae (G1+2) and one for multigravidae (G3+). The study requires 1665 women overall, including 1155 primi and secundigravidae and 500 multigravidae. It is designed to detect at least a 25% reduction in the primary endpoint consisting of a composite of small-for-gestational age (SGA), low birth weight or preterm birth in women in their first or second pregnancies, and at least a 50% decrease in placental malaria in women in multigravidae. The study will be open label as it will not be possible to blind the participants to their allocation, although where possible laboratory staff undertaking trial-related diagnostic tests will be blinded.

Antenatal clinic sites at Mpemba, Madziabango and Zingwangwa and Chileka will be involved. If less than half the required number of participants is recruited within the first half of the recruitment period, antenatal sites in neighbouring clinics in Blantyre, Zomba or Chikawa districts may be added.

Participants will be HIV-negative pregnant women. They will be screened for eligibility and given information about the study at their first contact with antenatal services before 28 weeks gestation and will be enrolled at 16 to 28 weeks gestation. The study is expected to start in the fourth quarter of 2010 or first quarter of 2011 and recruit for a period of 18 to 30 months, with a further six months follow-up.

Participants will be randomly allocated (see section 17.2 for description of the randomization process) to receive either at least three doses of IPTp with SP or at least three scheduled screenings with an RDT and treatment with DHA-PQ if they are RDT-positive. All participants will be given an insecticide-treated bed net if they do not already have one.

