#### **7.2.6 Inclusion of women treated for malaria and anaemia**

Women with symptoms of malaria at enrolment will not be excluded, but will be randomized to the study groups, and treated with the case-management drug, artemether-lumefantrine (CoArtem) if they fall in the IPTp-SP group. They will not receive SP that month, because lumefantrine is anticipated to provide post-treatment prophylaxis comparable with SP (3 to 4 weeks), based on recently completed treatment studies in pregnant women in Uganda. SP will then be provided at the next scheduled visit. Women randomized to the ISTp arm will already receive DHA-PQ as the treatment drug. DHA-PQ and CoArtem have comparable efficacy in treating malaria.

Women participating in the trial will receive all usual routine antenatal care, and will also be encouraged to attend the clinic if they feel unwell between appointments. As part of this package of care, women attending with symptoms consistent with malaria or anaemia will be tested and treated as appropriate, and continue in the study. No exclusions will be made relating to testing or treatment for these conditions, as the same care will be available equally to women in both study arms, and the same care would be provided if either intervention were introduced into usual practice.

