#### **7.2.7 Additional malaria testing not part of the point of care testing and treatment**

All participants who give consent will have a blood sample taken at enrolment and during the third trimester to test for peripheral malaria using standard microscopy of blood smears and PCR. The results of these tests will not become available until the end of the trial and will not be used to inform the care of the women. In this way, a point prevalence of malaria at baseline and in the third trimester can be estimated for both intervention arms, without contaminating the intervention in either arm. Testing of asymptomatic pregnant women is not usual practice in Malawi; the treatment of asymptomatic malaria in pregnancy has not yet been shown to be advantageous in women receiving IPTp; and women in the ISTp group will receive malaria testing and treatment if positive in any case; therefore no existing intervention will be withheld. This blood sample will be combined with a routine sample for haemoglobin in the third trimester, and with a second HIV screening test following the new WHO guidelines for repeat HIV testing in the third trimester.

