### 9.2 Secondary outcomes

#### 9.2.1 Secondary efficacy outcomes

1. Placental malaria (any species):
  - a. Past infection detected by histopathology
  - b. Active infection detected by:
    - i. Histopathology
    - ii. Microscopy
    - iii. Rapid diagnostic test
    - iv. Polymerase chain reaction (PCR)
2. Maternal malaria infection (peripheral blood) at delivery, detected by:
  - a. Microscopy
  - b. RDT
  - c. PCR
3. Peripheral malaria infection during pregnancy detected by:
  - a. Microscopy
  - b. PCR
4. Birth weight
  - a. Mean birth weight (grams)
  - b. Low birth weight (<2,500 grams)
5. Gestational age
  - a. Mean gestational age at birth (grams)
  - b. Pre-term birth (<37 weeks)
6. Small for gestational age
7. Maternal haemoglobin and anaemia:
  - a. At delivery
    - i. Mean maternal haemoglobin (g/dL)
    - ii. Anaemia (Hb ≤ 11 g/dL)
    - iii. Moderate to severe anaemia (Hb ≤ 8g/dL)

- b. During third trimester
    - i. Mean maternal haemoglobin (g/dL)
    - ii. Anaemia ( $Hb \leq 11$  g/dL)
    - iii. Moderate to severe anaemia ( $Hb \leq 8$ g/dL)
- 8. Miscarriage (loss of foetus before 28 weeks gestation)
- 9. Stillbirth (birth at 28 weeks or later showing no signs of life)
- 10. Composite endpoint of the primary endpoint plus fetal loss (miscarriage or stillbirths)
- 11. Infant death
  - a. Perinatal death (stillbirth or death within 7 days of birth)
  - b. Neonatal death (death within 28 days of birth)
- 12. Malaria infection of the newborn, detected by analysis of umbilical cord blood with:
  - a. RDT
  - b. Microscopy
  - c. PCR
- 13. Foetal haemoglobin and anaemia by sampling of umbilical cord blood at birth:
  - a. Mean foetal haemoglobin (g/dL)
  - b. Foetal anaemia ( $Hb \leq 12.5$  g/dL)
  - c. Moderate to severe foetal anaemia
- 14. Incidence of documented clinical malaria episodes during the second and third trimesters of pregnancy (history of fever in last 24 hours and documented malaria microscopy or RDT positive)
- 15. Presence of any evidence of malaria infection at term (last antenatal visit), identified through microscopy or PCR, or at delivery, identified through peripheral and placental RDT, microscopy or PCR, or placental histopathology (active or past infection).
- 16. Incidence of other illness episodes apparent at scheduled antenatal clinic visits or resulting in unscheduled clinic visits
- 17. Incidence and prevalence of clinical malaria in infants by seven days and six to eight weeks determined by:
  - a. RDT

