## **16.7 Unscheduled visits during pregnancy**

Participants will be encouraged to visit the clinic if they feel unwell between scheduled appointments.

Participants who present between appointments will be examined by study staff. Presenting symptoms, axillary temperature and blood pressure will be recorded. A finger-prick blood sample will be taken for Hb measurement and malaria RDT and thick and thin microscopy smears. Women presenting with serious adverse events possibly associated with DHA-PQ will have a 2 ml venous blood sample taken to measure blood drug levels. Any illness will be treated as appropriate and according to standard local care. The date of attendance, diagnosis and treatment will be recorded on the CRF, and any adverse events reported according to standard procedures.

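### Secondary outcome 14 counts clinical malaria already present at booking, which dilutes the arm contrast, and scheduled-visit testing may document mild febrile infections more often in the ISTp arm

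*Combined protocol and SAP*

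**What the plan says.** The objective in section 6.2.1 is "A decrease in the incidence of clinical malaria episodes in pregnancy". Item 14 of section 9.2.1 implements it as "Incidence of documented clinical malaria episodes during the second and third trimesters of pregnancy (history of fever in last 24 hours and documented malaria", and the case definition in full is "history of fever in last 24 hours and documented malaria microscopy or RDT positive". The item sets no start at randomisation, does not exclude the booking visit, and does not restrict the type of visit.

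Women "will be enrolled at 16 to 28 weeks gestation" (section 7.1). Section 7.2.6 adds: "Women with symptoms of malaria at enrolment will not be excluded, but will be randomized to the study groups".

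Testing differs by arm and by visit:

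- **Scheduled visits, ISTp.** RDT screening at each visit (sections 15.1, 16.1.3, 16.2.1, 16.4.1).
- **Scheduled visits, IPTp.** No routine point-of-care test. Section 7.2.7 explains: "Testing of asymptomatic pregnant women is not usual practice in Malawi". Section 7.2.6 provides for testing women with symptoms that suggest malaria, in both arms.
- **Stored research samples, both arms.** Blood for microscopy and PCR at booking and at the final antenatal visit, but not at the interim visits (sections 3.2, 7.2.7, 16.4.4).
- **Unscheduled visits, both arms.** "A finger-prick blood sample will be taken for Hb measurement and malaria RDT and thick and thin microscopy smears" (section 16.7).

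**The concern.** Two separate things can distort the comparison.

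**Booking episodes.** A woman who is febrile and infected when she books became ill before either strategy could act. Her episode carries no information on efficacy, yet it enters the count in whichever arm she is allocated to.

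**Unequal documentation at scheduled visits.** An ISTp woman who mentions a mild fever already has an RDT result, so an incidental infection makes her a case. An IPTp woman with the same history is a case only if someone judges her symptomatic and tests her. Staff and women know the allocation, because blinding covers laboratory tests only (section 7.2.3).

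At stake is the reading of a named secondary objective. Both effects work against ISTp, so a real reduction in clinical malaria could be understated or missed. The second effect could also suggest an increase where there is none.

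**Working it through.** The plan gives no expected rate, sample size or power for item 14, so there is no plan figure to reproduce for it. The rates below are illustrations on assumed values.

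**1. Dilution by booking episodes**

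Let b be the share of control-arm episodes that arise at booking, and RR the true relative risk (ISTp/IPTp) afterwards. With equal detection, booking episodes are balanced by randomisation, so:

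observed RR = b × 1 + (1 − b) × RR

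With RR = 0.75 and b assumed:

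| b | Calculation | Observed RR |
|---|---|---|
| 0 | 0.75 | 0.75 |
| 0.2 | 0.2 + 0.8 × 0.75 | 0.80 |
| 0.4 | 0.4 + 0.6 × 0.75 | 0.85 |
| 0.6 | 0.6 + 0.4 × 0.75 | 0.90 |

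Starting the count after booking sets b to 0 and returns 0.75.

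**2. Where testing can differ for a woman who meets the fever criterion**

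| Visit | ISTp | IPTp | Stored smear, both arms |
|---|---|---|---|
| Booking | RDT for all | If judged symptomatic | Yes |
| Interim | RDT for all | If judged symptomatic | No |
| Final antenatal | RDT for all | If judged symptomatic | Yes |
| Unscheduled | RDT and smears | RDT and smears | Not needed |

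The case definition uses a fever history over 24 hours. The scheduled symptom questions cover the last month (section 16.1.5) or the time since the first visit (sections 16.2.3 and 16.4.3). No section says that a 24-hour fever history leads to a test in the IPTp arm, or whether the stored smears count toward item 14. The gap is therefore widest at the interim visits.

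**3. What unequal documentation could do**

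Let s be the share of true cases that arise at scheduled visits, and q the chance that such a case is tested in the IPTp arm. With no true effect:

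observed RR = 1 / (q × s + 1 − s)

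| q | s = 0.25 | s = 0.50 | s = 0.75 |
|---|---|---|---|
| 1 | 1.00 | 1.00 | 1.00 |
| 0.75 | 1.07 | 1.14 | 1.23 |
| 0.5 | 1.14 | 1.33 | 1.60 |

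Neither s nor q is in the documents.

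**4. Scale in episodes**

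- Women per arm: 1655 / 2, about 827 (sections 17.1 and 17.2).
- RDT positivity per visit: section 7.2.11 expects 20% to 30% of ISTp women to be treated at some point. Over three visits, assuming independence, 1 − 0.80^(1/3) = 7% and 1 − 0.70^(1/3) = 11%. Take 10%.
- Fever in the last 24 hours, unrelated to infection: 5% to 10%, assumed.
- IPTp women with such a fever who go untested: half, assumed.

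Excess ISTp episodes per interim visit = 827 × 0.10 × (0.05 to 0.10) × 0.5 = about 2 to 4. If all such women are tested, the last factor is 0 and so is the excess.

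**The case against.** The strongest reply is that item 14 requires fever, so infections without symptoms never count in either arm, and that the protocol already deals with febrile women alike. Section 7.2.6 has symptomatic women tested in both arms. Section 15.1.1 covers women in either group who attend a scheduled visit with fever and confirmed malaria. Sections 16.1.3 and 16.2.1 reserve the scheduled SP dose or RDT screen for women without symptoms.

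Much of this stands. It rules out the reading that a febrile IPTp woman is, by design, given SP untested. It does not close the gap. Section 15.1.1 governs treatment once malaria is confirmed and does not say when a test is done. The trigger in section 7.2.6 is a judgement about symptoms, whereas the case definition is any 24-hour fever history. What remains is a risk confined to fever histories that prompt no test in the IPTp arm.

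A reader might also infer that only unscheduled visits give comparable data and should carry the main comparison. The documents do not support that. Both arms have stored smears at booking and at the final visit. Restricting the outcome to unscheduled visits would make it depend on care-seeking, and section 7.2.11 itself notes that women will differ in what they know of their malaria status and treatment. It would also drop genuine febrile malaria found at scheduled visits.

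The objection does not touch the booking point. No section starts the count after the first intervention.

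**Conclusion.** The booking part follows from the text as written: item 14 includes episodes that precede any intervention, and they dilute the contrast. The size depends on the unknown share of episodes at booking. The range of 0.80 to 0.90 for a true RR of 0.75 rests on assumed shares of 20% to 60% and on equal detection.

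The detection part is a credible risk, chiefly at interim visits. Its size cannot be computed from the documents, which give no fever prevalence and no IPTp testing rate.

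Three stronger readings are not supported:

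- **That booking cases inflate the ISTp arm.** Randomisation balances them. They could add to ISTp only through unequal detection, and both arms have a stored smear at that visit.
- **That a definite excess can be stated.** Applying the assumptions of step 4 to three scheduled visits gives about 6 to 12 ISTp episodes. That figure rests wholly on half of the matching IPTp women going untested, which has no source and sits badly with sections 7.2.6 and 15.1.1.
- **That the trial's main conclusion is at risk.** Both primary endpoints are assessed at birth or delivery. The non-inferiority fallback in section 17.3.3 covers only adverse outcome and placental malaria. Both distortions run against ISTp, so they would not produce a false superiority claim on item 14.

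This is a cheap and worthwhile correction to one secondary outcome.

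**What to change.** 1. In section 9.2.1, item 14, count only episodes after the booking visit. Report episodes present at booking as a baseline characteristic. Keep all post-booking episodes, from scheduled and unscheduled visits, in the main comparison.
2. Ask the same 24-hour fever question at every scheduled visit in both arms, and record the answer before any RDT is read. This does not in itself equalise testing, but it shows how many IPTp women with a fever history had no test.
3. In section 17.3.3, add a sensitivity analysis limited to episodes at unscheduled visits, where both arms have RDT and smears.
4. Use the blinded final-visit smears, combined with the recorded fever answer, as an equal-testing check at that visit. Use the smear alone in both arms, since ISTp women also have an RDT there.

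The cost is a change of outcome wording, one CRF item with a fixed recording order, slightly fewer counted episodes, and a little more analysis. No new sample is needed and care does not change.

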### 9.2.2 Safety outcomes

- 1. Severe cutaneous skin reaction in the mothers within 30 days of drug intake
- 2. Other serious adverse events in the mothers
- 3. Congenital malformations identified by six weeks after birth
- 4. Neonatal jaundice within 24 hours and at seven days
- 5. Laboratory test results outside of normal range

### 9.2.3 Tolerability outcomes

1. Non-serious adverse events in the mothers
2. Adherence to study medication

### 9.2.4 Immunology outcomes

Concentration of antibodies known to be associated with protection against malaria in pregnancy and in general, including antibodies recognizing variant surface antigens on *P. falciparum* infected erythrocytes that block parasite adhesion to chondroitin sulphate A.

### 9.2.4 Economic outcomes (sub-study)

The economics sub study will be conducted alongside the main clinical trial. Health facility and exit surveys will be carried out to estimate the costs of the intervention to the health services and households respectively. To capture costs incurred during the first six to eight weeks after delivery, including the costs of caring for low birth weight babies, questions about use of health services will be integrated into the clinical health assessment at six weeks.

The specific outcomes of the economics sub-study are:

1. Costs of the two intervention arms to the health facility and household up to six to eight weeks after delivery. Household data will be collected by questionnaire at the six-week clinic visit; health facility data directly from the health facility.
2. Cost-effectiveness of ISTp-DP versus IPTp-SP measured in terms of cost per each of the following endpoints averted, which are measured in the main trial:
  - Adverse birth outcome (still birth, preterm birth or low birth weight)
  - Active and past malaria infection of the placenta (detected by histopathology, microscopy or RDT)
  - Maternal anaemia
  - Peripheral malaria at delivery
  - Neonatal deaths

Cost per disability adjusted life year (DALY) averted will be estimated using the cost data collected and effectiveness data generated by the trial, with necessary adjustments made to the DALY to accommodate outcomes in pregnant women and their newborns.

The household and facility data from the cost and cost-effectiveness analysis will be used (alongside data from other studies) to populate a model of the economic burden of malaria in pregnancy. In addition, they will be used to:

- Model the long-term costs and consequences of malaria in pregnancy to the household and health facility in both trial arms, and to
- Model the costs of scaling up the intervention at regional/national level and investigate affordability in Malawi.

### 9.2.5 Acceptability, feasibility, implementability and scale up: outcomes

The overall aim of this sub study is to explore the acceptability, feasibility, implementability and potential for scale-up of ISTp-DP. The main outcomes are more specifically:

- Social, cultural and economic determinants of demand, access and use for malaria in pregnancy interventions.
- Acceptability of ISTp for provider and user.
- Preferences for malaria in pregnancy interventions at the user and provider level.
- Factors at facility and district levels which influence the delivery of malaria in pregnancy interventions and in particular the feasibility and implementability of ISTp in the context of other reproductive health interventions (e.g. prevention of mother to child transmission).
- Major barriers to the scale-up and use of interventions to control malaria in pregnancy, specifically of ISTp.

## 10 Screening and eligibility assessment

Potential participants will be screened for eligibility when attending their first routine antenatal appointment. If they meet the inclusion criteria they will be offered enrolment following informed consent. Women who do not meet the inclusion criteria, or who do not wish to participate in the trial, will receive usual antenatal care, including the standard IPTp-SP schedule.

Eligibility screening will be conducted by clinic nurses and midwives and supported by study staff. Screening data will be recorded in a log that will be kept in the investigators site file. One screening log will be kept per site. This record will be used to report how many women attended for antenatal appointments, how many were potentially eligible, how many were enrolled into the study, and reasons for non-eligibility of those not enrolled. It will be used to ensure that women are selected for the study without bias. Each screened woman will be assigned a screening registration number in sequential order by the study clinic. Screened attendees who do not meet the eligibility criteria for the trial will be considered screening failures, in which case the registration number will not be re-used; however the woman can re-enter the study at a later date if she meets the eligibility criteria at that visit.

Gestational age will initially be estimated first using a combination of fundal height as measured by the midwife and last menstrual period (LMP) dates provided by the woman, where available. Women attending antenatal care for the first time after 28 weeks gestation will be excluded from the trial. Women attending before 16 weeks gestation will be screened for inclusion, given information about the trial and enrolled when they next attend between 16 and 28 weeks gestation. Women who are eligible and express an interest in the trial may receive an ultrasound scan at this point, using portable equipment to accurately assess the gestational age of the pregnancy and identify multiple gestations. Alternatively the scan may be done at another appointment shortly after enrolment. The ultrasound scan will be done by a trained clinician who is part of the study team. Any women identified as having multiple gestations will be excluded from the study. Ultrasound scans are not part of routine antenatal care in Malawi; the equipment will be specially purchased and study staff trained to use it.

Women already known to be HIV-positive will be automatically excluded from the study. All women will be offered HIV counselling and testing using rapid diagnostic tests, and if they refuse or are found to be positive will be excluded from the trial and offered co-trimoxazole

prophylaxis. Refusal to be tested is very rare at these clinics (<1%). For women presenting before 16 weeks gestation, HIV testing will be performed as part of usual care before the woman is invited to join the study, using a finger-prick blood sample. For women presenting between 16 and 28 weeks, HIV testing will be undertaken using a venous blood sample that will be used for both routine and study-specific tests. As venous sampling would not normally be included as part of care, consent for screening would be obtained before this blood draw.

All potentially eligible women will be tested for anaemia. If they are found to be severely anaemic ( $Hb \leq 7$  g/dL) they will be excluded from the trial and referred to the nearest hospital for blood transfusion. If a woman with severe anaemia is successfully treated and attends the clinic again before 28 weeks gestation, she will become eligible for the trial provided that she meets all other inclusion criteria. Women with less severe anaemia will be included in the study and their anaemia treated by treating any cause identified and with ferrous sulphate 200-400mg twice daily for 2-3 months.

Women will be asked whether they plan to travel or migrate outside of the study area (to be defined for each site before the start of the trial) during the follow-up period. Women who plan to travel outside of the study area will be excluded.

Women who are found to be ineligible after they have signed their informed consent will be excluded from the trial but will continue to receive all study-specific benefits, if she wishes to (e.g. missed twin pregnancies).

